**Clinical outcomes**				
*Primary outcome*				
Duration of mechanical ventilation	Increased number of ventilator-free days in treatment group	Number of ventilator-free days	Duration of ventilation at time of randomization	*t* test, linear regression
*Secondary outcomes*				
Duration of mechanical ventilation	Decreased duration of mechanical ventilation in treatment group	Duration of mechanical ventilation (days)	Duration of ventilation at time of randomization	*t* test, linear regression
Episodes interrupting treatment with furosemide	Fewer episodes of interruption in treatment group	Number of episodes	None	*t* test
Need for dialysis	Smaller proportion of patients requiring dialysis in treatment group during ICU stay	Proportion of patients requiring dialysis during 30 days	None	Chi-squared or Fisher’s exact statistic
Length of ICU stay	Shorter length of stay in treatment group	Duration of ICU stay	Duration of ICU stay at time of randomization	*t* test, linear regression
ICU mortality	Decreased ICU mortality in treatment group during ICU stay	All-cause mortality (binary)	APACHE-2 and SOFA scores at randomization	Kaplan-Meyer survival curve (time to death)
30-day mortality	Decreased 30-day mortality in treatment group	All-cause mortality (binary)	APACHE-2 and SOFA scores at randomization	Kaplan-Meyer survival curve (time to death)
*Physiologic outcomes*				
Change in oxygenation	Greater increase PaO_2_/FiO_2_ ratio in treatment group at day 3 and day 5	Change in PaO_2_/FiO_2_ ratio	None	*t* test
	Greater decrease in oxygenation index in treatment group at day 3 and day 5	Change in oxygenation index	None	*t* test
Change in lung compliance	Greater increase in dynamic compliance in treatment group at day 3 and day 5	Change in dynamic compliance during study treatment (ml/cmH_2_O)	None	*t* test
Change in fluid balance	Greater net decrease in fluid balance in treatment group at day 3 and day 5	Change in net fluid balance (ml)	Net fluid balance at time of randomization	*t* test, linear regression
Change in body weight	Greater decrease in body weight in treatment group at day 3 and day 5	Change in body weight (kg)	Baseline weight	*t* test, linear regression
Urine output	Greater net urine output in treatment group at day 3 and day 5	Urine output during 3 days of study treatment (ml)	Net fluid balance at time of randomization	*t* test, linear regression

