Dose of furosemide	Lower total amount of furosemide used in treatment group at day 3	Dose of furosemide during 3 days of study treatment (mg)	None	*t* test
Changes in serum albumin	Greater increase in serum albumin level in treatment group at day 3 and day 5	Change in serum albumin (g/l)	None	*t* test
Changes in colloid osmotic pressure	Greater increase in colloid osmotic pressure in treatment group at day 3 and day 5	Change in colloid osmotic pressure (mmHg)	None	*t* test
Changes in serum total protein	Greater increase in total protein in treatment group at day 3 and day 5	Change in total protein (g/l)	None	*t* test
Change in electrolytes	No difference between study groups for major electrolytes (sodium, potassium) at day 3 and day 5	Change in electrolytes between beginning and end of study treatment (mEq/l)	None	*t* test

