**Sensitivity analyses**				
Per-protocol analysis		All outcomes	None	
Adjusting for baseline covariates		All outcomes	As described	Multivariable regression
Adjusted for dose of furosemide	Treatment with albumin results in improvement beyond that explained by dose of furosemide	All outcomes	Dose of furosemide	Multivariable regression

APACHE-2, Acute Physiology and Chronic Health Evaluation-2; ARDS, acute respiratory distress syndrome; FiO_2,_, fraction of inspired oxygen; ICU, intensive care unit; PaO_2_, partial pressure of oxygen in arterial blood; SOFA, Sepsis-related Organ Failure Assessment.

**Table 3 T3:** Feasibility outcomes and estimated sample sizes

**Outcome**	**Demonstration of feasibility**	**Estimated actual proportion**	**Desired precision**	**Required sample size**
Administration of first dose of albumin within two hours of furosemide administration	Lower-bound of 95% confidence interval greater than 85%	0.925	0.075	47
Administration of at full 72 hours of study treatment	Lower-bound of 95% confidence interval greater than 80%	0.9	0.1	34
Absence of hyperoncotic albumin in control arm	Lower-bound of 95% confidence interval greater than 85%	0.95	0.1	18
Randomization rate of patients eligible by screening criteria	Lower-bound of 95% confidence interval greater than 50%	0.65	0.15	39

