### Participants

The target population is one of critically ill adults with hypoalbuminemia who are in a recovery phase of critical illness and judged by the treating physician to be volume overloaded, based on clinical findings, such as peripheral edema, delayed weaning, or chest radiographic findings of interstitial or pleural fluid. Thus, inclusion criteria include: (1) admission to ICU; (2) age ≥ 18 years; (3) hemodynamic stability for at least 24 hours, defined as the absence of persistent (>1 hour) hypotension (systolic blood pressure < 90 mmHg) and tachycardia (heart rate >110), not currently on vasopressors, received less than 2 l crystalloid or colloid boluses or two units of packed red blood cells, maintenance fluids excluded; (4) hypoproteinemia, defined as serum albumin < 30 g/l, or total protein < 60 g/l; (5) clinical decision by the caregiving team to diurese at least 3 l of net fluid balance within the next 72 hours, for any reason.

Patients will be excluded for any of the following reasons: (1) known pregnancy; (2) patient or surrogate decision maker unable or unwilling to consent to blood product administration, including albumin; (3) acute kidney injury (RIFLE criteria ‘F’ or greater with either tripling of creatinine or creatinine >355 μmol/l (with a rise of >44) or average urine output below 0.3 ml/kg/hour for 24 hours) without any improvement in the previous 24 hours, or otherwise expected to necessitate dialysis within 48 hours in the opinion of the treating physician; (4) chronic kidney injury requiring dialysis; (5) clinically documented cirrhosis; (6) clinically documented nephrotic syndrome; (7) serum sodium levels greater than 150 mEq/l or serum potassium levels less than 2.5 mEq/l that cannot be treated prior to administration of study treatment; (8) inability to measure urine output and fluid balance accurately; (9) receipt of hyperoncotic albumin within preceding 24 hours; (10) previous enrollment in this trial, or any other research studies for which co-enrollment is not permitted; (11) estimated survival or ICU stay less than 72 hours.

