**Assessments**								
*Baseline variables*								
Demographics	×							
Past medical history	×							
Type of diagnosis on admission	×							
APACHE-2 score at randomization	×							
SOFA score at randomization	×							
Diagnosis of ARDS at randomization	×							
Time since hemodynamic stability	×							
Length of ICU stay at randomization	×							
*Laboratory results*								
Renal function tests			×	×	×	×	×	
Serum chemistry			×	×	×	×	×	
Serum albumin levels			×	×	×	×	×	
Serum total protein levels			×		×		×	
Colloid osmotic pressure			×		×		×	
Blood gas analysis			×	×	×	×	×	
Troponin I levels			×	×	×	×	×	
Serum lactate levels			×	×	×	×	×	
Complete blood count			×	×	×	×	×	
*Physiologic data*								
Vital signs			×	×	×	×	×	
Glasgow Coma Scale rating			×	×	×	×	×	
Weight			×	×	×	×	×	
Ventilator data			×	×	×	×	×	
Fluid intake and output			×	×	×	×	×	
Diuretic doses and timing			×	×	×	×	×	
*Clinical outcomes*								
Study treatment held?			×	×	×	×	×	
Need for dialysis?			×	×	×	×	×	×
Hypotension requiring fluids			×	×	×	×	×	
Hypotension requiring vasopressors			×	×	×	×	×	
Suspected infection?			×	×	×	×	×	
Intubation status			×	×	×	×	×	×
Date of transfer from ICU			×	×	×	×	×	×
Date of death			×	×	×	×	×	×

APACHE-2, Acute Physiology and Chronic Health Evaluation-2; ARDS, acute respiratory distress syndrome; ICU, intensive care unit; SOFA, Sepsis-related Organ Failure Assessment.

Alternatively, if a treating physician believes that a patient might qualify for the study, and is in urgent need of diuresis, the patient can be considered for deferred consent. To be eligible for deferred consent, patients or surrogate decision makers must have already given consent for administration of blood products. Patients will then be randomized to a study arm and diuretics administered. Study investigators will try to obtain consent from the surrogate decision maker within the next 48 hours. If the surrogate decision maker cannot be located, the patient will be withdrawn from the study. Similarly, if the surrogate decision maker declines participation in the study, the participant will be withdrawn from the study. The deferred consent process is only to be used if the need for diuresis is urgent, and the surrogate decision maker cannot be reached in a timely fashion.

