### Statistical methods

All *P* values will be two sided, with a level of *P* ≤ 0.05 indicating statistical significance. All data will be analyzed using statistical software on an intention-to-treat basis. All randomized participants, regardless of protocol adherence, will be included in the main analysis.

Feasibility outcomes will be calculated as proportions with 95% confidence intervals, with feasibility being met if the lower-bound of the 95% confidence interval is above the level pre-specified for feasibility (Table 
3). Data regarding our primary and secondary clinical outcomes will also be collected during this pilot study for future analysis; however, no analysis of clinical outcomes will be made for this pilot study, as the main purpose is to inform the definitive trial. Data collected from this pilot study will remain blinded and eventually incorporated into the dataset for the definitive trial, with the following pre-specified analyses.

Comparisons between the two treatment groups at a single time point (for example, baseline variables, number of patients requiring fluid bolus or vasopressors for hypotension, total dose of furosemide, and so on) will made using unpaired Student’s *t* test. Comparisons within a treatment group at different time points (change in serum albumin, colloid osmotic pressure, total protein, weight, fluid balance, oxygenation, lung compliance at day 3 and day 5, and so on) will be analyzed in a similar fashion. Multiple between-groups comparisons of continuous variables will be analyzed by repeated-measures analysis of variance. Linear regression will be used where appropriate to correct for baseline variables. Ventilator-free days will be defined as the number of 24-hour periods in which a patient does not need ventilation during 28 days (patients who die, by definition, will have 0 ventilator-free days). Survival analysis will be performed to assess 30-day mortality.

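### Total furosemide dose is compared by an unadjusted t test although baseline renal function is available and can vary widely: a small, avoidable loss of precision in a secondary outcome

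*Protocol article*

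**What the plan says.** In the protocol article, Table 2 (physiologic outcomes) defines the outcome as "Dose of furosemide during 3 days of study treatment (mg", enters *None* under covariates and gives a t test as the method. The Statistical methods section repeats this choice by listing total furosemide dose among its examples for the unpaired t test. Other rows do name covariates: urine output and fluid balance carry "Net fluid balance at time of randomization", and the two mortality rows carry "APACHE-2 and SOFA scores at randomization". No row names a renal measure.

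Two general provisions bear on this. The sensitivity row "Adjusting for baseline covariates" covers all outcomes, but only with the covariates already described in the table. Statistical methods adds: "Linear regression will be used where appropriate to correct for baseline variables". It names no variable.

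On renal function, exclusion 3 (Participants) removes patients in RIFLE class F only if they are "without any improvement in the previous 24 hours, or otherwise expected to necessitate dialysis within 48 hours". Exclusion 4 removes chronic kidney disease only where dialysis is required. Table 4 lists "Renal function tests" on days 1 to 5, outside its baseline block. Data collection describes a renal profile taken at least daily in patients undergoing diuresis, within a data window that opens at ICU admission.

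**The concern.** The protocol itself ties kidney function to how much furosemide is given. Interventions has study treatment held for new or worsening kidney injury while the team also holds furosemide, and Outcomes gives renal failure as an example of what interrupts furosemide. Outcomes also says that dose is recorded to learn whether study treatment improves the physiologic response to the diuretic. Spread in kidney function blurs exactly that question.

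Eligibility runs from normal renal function to improving RIFLE F injury. If function at entry predicts the three-day dose, a plain t test leaves that spread in the error term, and the confidence interval is wider than the collected data require. What is at stake is the precision of one secondary physiologic comparison, not its validity.

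**Working it through.** **The plan's own figures.** The document gives no standard deviation, effect size, power or sample size for furosemide dose. Its only sample size basis is first-dose adherence (Table 3: proportion 0.925, precision 0.075). That reproduces: 1.96² × 0.925 × 0.075 / 0.075² = 47.4, against a stated 47. Nothing in this calculation depends on the point raised here.

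**Does any provision already supply a renal covariate?**
- The Table 2 row says *None*.
- The sensitivity row uses the covariates as described, which for this row is none.
- The sentence on linear regression could reach furosemide dose, but it fixes no variable, and the same section assigns this outcome to the t test.

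So an unadjusted test is the stated choice.

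**Is a baseline value available?** Exclusion 3 has creatinine criteria, so a value is needed at screening, and data are collected from ICU admission. Table 4 starts renal tests on day 1, so the plan must say which value counts as baseline.

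**Size of the gain.** Let rho be the correlation within arm between baseline renal function and dose. This is an assumption; the document gives no value.
- Large-sample variance factor after adjustment: 1 − rho².
- With one covariate and n = 50 (the pilot target), multiply by (n − 3)/(n − 4) = 47/46 = 1.022.
- Equivalent number of patients: 50 divided by the n = 50 factor.
- Large-sample power of a comparison that has 80% unadjusted: Phi(2.80/√(1 − rho²) − 1.96).

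| rho | 1 − rho² | Fall in variance | Factor at n = 50 | Equivalent patients | Power from 80% |
|---|---|---|---|---|---|
| 0.1 | 0.99 | 1% | 1.01 | 49 | 80% |
| 0.2 | 0.96 | 4% | 0.98 | 51 | 82% |
| 0.3 | 0.91 | 9% | 0.93 | 54 | 84% |
| 0.5 | 0.75 | 25% | 0.77 | 65 | 90% |
| 0.6 | 0.64 | 36% | 0.65 | 76 | 94% |

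At n = 50 the break-even is 1 − rho² = 46/47, that is rho = √(1/47) = 0.15. Below that, adjustment costs at most about 2% in variance. In a larger trial this cost all but disappears.

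**The case against.** The strongest reply is that nothing here is an error. A t test on a randomized outcome is valid, and a condensed article may leave extra covariates to a fuller plan. The first part stands. The second is weaker: Table 2 has a covariates column, fills it for other outcomes and enters *None* here, and Statistical methods calls these analyses pre-specified.

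A second reply is that the gain is hypothetical. This also stands. Dose is set by the caregiving team, who aim to remove at least 3 l net, so other drivers may dominate. Poor renal function may also act both ways: holding furosemide lowers the total, while a weak response may raise it. The linear correlation could therefore be small.

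A third reply is that the pilot is unaffected. Statistical methods defers clinical analyses to the definitive trial, and under Dissemination policy outcomes by treatment group are published from the pilot only if non-feasibility is shown. That limits the point to those two uses.

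A reader might carry the argument over to the dialysis row ("Proportion of patients requiring dialysis during 30 days", also with no covariate). The documents do not support that. Chronic dialysis and expected early dialysis are excluded, so events should be few. In simulations of 1,500 runs per setting (assumed control risk 5% to 20%, treatment odds ratio 0.5, covariate log-odds ratio 0.7 or 1.4 per SD), the adjusted logistic model at N = 50 failed in about 67% of runs at 5% risk, 28% at 10% and 4–5% at 20%. Where it fitted at 10% risk, the standard error of the log-odds ratio rose from 1.16 to 1.20–1.28, and power did not improve. At an assumed N = 500 that standard error still rose; power gained about 2 to 10 points, and the variance ratio on the risk difference was 0.85 to 0.99. A modest gain in a larger trial is thus possible, but it rests on a trial size and event risks that the document does not give.

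A reader might also cite chance imbalance. At 25 per arm, a gap above 0.5 SD has probability 2 × (1 − Phi(0.5/√(2/25))) = 0.077. But the pilot is not normally analysed by arm, and at an assumed 300 per arm the same gap is 0.5/√(2/300) = 6.1 standard errors.

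**Conclusion.** The point holds for furosemide dose, at low severity. The plan fixes an unadjusted test for an outcome that it links to kidney function itself, in a cohort whose renal function may vary widely, with a suitable baseline measure available. The fall in variance is about 4% to 36% for assumed correlations of 0.2 to 0.6, and there is a negligible loss near 0.1 at pilot size. All of this rests on a correlation that the document does not report.

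Three stronger readings should not be drawn:
- The comparison is not biased.
- The feasibility conclusion is not affected.
- It would be too much to say that the plan ignores kidney function altogether. No renal measure is named as a covariate, but APACHE-2 and SOFA may carry renal information into the mortality rows, and the general regression sentence leaves some room.

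**What to change.** In the furosemide dose row of Table 2, replace *None* with serum creatinine, defined as the last value before randomization on the log scale, and replace the t test with linear regression on treatment and that covariate. Remove total furosemide dose from the t test examples in Statistical methods so that the two places agree. State that this applies to the definitive trial and to any pilot report by treatment group.

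Optionally, add the same covariate to the urine output row, which already lists linear regression and net fluid balance. Leave the dialysis row as it is.

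The cost is two table cells, one sentence and one degree of freedom, with no new measurement. The case report form must identify the pre-randomization creatinine, because Table 4 begins renal tests on day 1. The change is best made before any outcome is seen by treatment group; the article says recruitment had not begun.

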**Subgroup analyses**				
ARDS	Improved oxygenation in patients with ARDS		None	Regression methods with appropriate interaction term
Severity of disease	Improved hemodynamic stability in patients with severe disease		None	Regression methods with appropriate interaction term
Time since recovery of hemodynamic stability	Improved hemodynamic stability in patients with recent hemodynamic instability	>48 hours versus <48 hours of hemodynamic stability (as defined by study eligibility criteria)	None	Regression methods with appropriate interaction term
**Sensitivity analyses**				
Per-protocol analysis		All outcomes	None	
Adjusting for baseline covariates		All outcomes	As described	Multivariable regression
Adjusted for dose of furosemide	Treatment with albumin results in improvement beyond that explained by dose of furosemide	All outcomes	Dose of furosemide	Multivariable regression

APACHE-2, Acute Physiology and Chronic Health Evaluation-2; ARDS, acute respiratory distress syndrome; FiO_2,_, fraction of inspired oxygen; ICU, intensive care unit; PaO_2_, partial pressure of oxygen in arterial blood; SOFA, Sepsis-related Organ Failure Assessment.

**Table 3 T3:** Feasibility outcomes and estimated sample sizes

**Outcome**	**Demonstration of feasibility**	**Estimated actual proportion**	**Desired precision**	**Required sample size**
Administration of first dose of albumin within two hours of furosemide administration	Lower-bound of 95% confidence interval greater than 85%	0.925	0.075	47
Administration of at full 72 hours of study treatment	Lower-bound of 95% confidence interval greater than 80%	0.9	0.1	34
Absence of hyperoncotic albumin in control arm	Lower-bound of 95% confidence interval greater than 85%	0.95	0.1	18
Randomization rate of patients eligible by screening criteria	Lower-bound of 95% confidence interval greater than 50%	0.65	0.15	39

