**Methods/Design:**

FADE is a single-center, parallel, pilot randomized controlled trial. We aim to allocate 50 hemodynamically stable, hypoalbuminemic adult patients receiving diuresis to treatment with either 100 ml of either 25% albumin or normal saline placebo twice daily, for a total of six doses. Diuretics are to be prescribed by the caregiving team at least twice daily, and administered within 2 hours following study treatment. Patients, intensive care unit (ICU) clinicians, data collectors, and outcome adjudicators will be blinded to treatment allocation. Feasibility outcome measures include the proportion of patients receiving albumin within 2 hours of diuretic, the proportion of patients receiving the full six doses of study treatment, the proportion of patients who receive open label 25% albumin, and the rate of recruitment. Physiologic, laboratory, and clinical data are collected until discharge from the ICU or until 30 days.

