### Recruitment plans and consent process

The study will be carried out at two different ICUs within a single tertiary care academic center (Hamilton General Hospital and the Juravinski Hospital and Cancer Centre, Hamilton, Ontario, Canada). Both sites are research-intensive and serve a high volume of general medical and surgical critically ill patients. The recruitment process is outlined in Figure 
1 and Table 
4. Patients will be screened by study investigators within 72 hours of admission to the ICU. Patients present in the ICU for longer than 72 hours can be referred to study investigators by the team providing care if they believe that the patient might qualify for the study. Patients or surrogate decision makers will be approached by the research team and informed of the study rationale and methods, and provided with literature about the study. They will then be given an opportunity to consider study enrollment, in person or via phone. If the patient is willing, consent for the research study as well as blood product administration, if it has not already been received by the caregiving team, will be obtained. Patients will be screened and randomized once the caregiving team decides diuresis is necessary, but prior to administering diuretics from the caregiving team.

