The secondary clinical outcomes that we will collect data for include: (1) duration of mechanical ventilation, measured from time of randomization until extubation that is successful for 24 hours or more, recorded in days; (2) number of episodes of interrupting treatment with furosemide (for example, hypotensive episodes, renal failure, contraction alkalosis); (3) proportion of patients receiving dialysis; (4) length of ICU stay from randomization; (5) ICU mortality; and (6) 30 day mortality. We hypothesize that the addition of 25% albumin will lead to fewer interruptions of diuresis, a reduced incidence of acute kidney injury, and a shorter stay in the ICU.

The secondary physiologic outcomes that we will collect data for include: (1) changes in oxygenation (FiO_2_, PaO_2_/FiO_2_ ratio, oxygenation index) from baseline at day 3 and day 5; (2) changes in dynamic lung compliance, reflecting changes in extravascular lung water, at day 3 and day 5; (3) changes in total fluid balance and body weight, and amount of urine output from baseline at day 3 and day 5; (4) total dose of furosemide used, to assess whether study treatment improves the physiologic response to furosemide; (5) changes in serum albumin and colloid osmotic pressure between treatment groups from baseline at day 3 and day 5, to ensure that the experimental treatment results in the expected increases in these measurements; (6) changes in electrolyte levels (potassium level less than 2.5 mEq/l, sodium level >150 mEq/l), as a way to ensure that no major, potentially harmful changes in serum electrolytes occur as a result of study treatment.

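### The furosemide-adjusted row in Table 2 conditions on a post-randomisation dose that albumin is expected to change, so it is not a sensitivity check of the randomised comparison

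*Protocol article*

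**What the plan says.** The sensitivity block of Table 2 contains the row "Adjusted for dose of furosemide". It applies to every outcome, uses multivariable regression, names furosemide dose as its only covariate, and gives the hypothesis "Treatment with albumin results in improvement beyond that explained by dose of furosemide". A separate row just above it covers adjustment for baseline covariates.

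Elsewhere the article treats the same dose as a result of treatment:

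- The physiologic block of Table 2 has furosemide dose as an outcome, in mg over the three treatment days, with the hypothesis "Lower total amount of furosemide used in treatment group at day 3".
- The Outcomes section lists as a secondary physiologic outcome "total dose of furosemide used, to assess whether study treatment improves the physiologic response to furosemide".
- The secondary clinical block of Table 2 expects, for furosemide treatment, "Fewer episodes of interruption in treatment group".

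On timing, Recruitment plans and consent process states: "Patients will be screened and randomized once the caregiving team decides diuresis is necessary, but prior to administering diuretics from the caregiving team". On control of the dose, the Abstract states: "Diuretics are to be prescribed by the caregiving team at least twice daily". No dose is fixed. Interventions and Outcomes both foresee furosemide being held or interrupted, for example for hypotension or renal failure.

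Statistical methods makes the main analysis intention to treat and defers the analysis of clinical outcomes to the definitive trial.

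**The concern.** A sensitivity analysis should ask whether the randomised comparison survives a change in assumptions. This row asks something else. It holds fixed a variable that arises after randomisation and that the plan itself expects to differ by arm. Two things follow.

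- Any part of the albumin effect that runs through furosemide dose is taken out, so the coefficient is no longer the total effect.
- If something uncontrolled, such as severity or diuretic resistance, affects both dose and outcome, patients with equal doses in the two arms are no longer comparable. The coefficient then mixes a direct effect with confounding that randomisation does not remove.

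The stated conclusion is a direct-effect claim, and ordinary regression on dose supports it only without such common causes. At stake is how the definitive trial's results are read. A row labelled as sensitivity invites a reader to treat agreement as confirmation and disagreement as doubt, and neither inference would be sound.

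**Working it through.** The plan gives no figure on this point, so there is none to reproduce. The check is structural, with a numerical illustration.

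**Structure, from the text**

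1. Is the covariate measured after randomisation? Yes. The only defined dose covers the three treatment days, and randomisation precedes the diuretic. The deferred-consent route has the same order. Table 4 schedules diuretic doses from Day 1.
2. Is it expected to depend on arm? Yes. A lower dose is hypothesised with albumin. Fewer interruptions, also hypothesised, could raise the dose, so the net shift could go either way.
3. Does it depend on the patient's condition? The caregiving team sets it, and the listed reasons for interruption are clinical deteriorations. That severity drives dose is an inference from this, not a statement in the article.
4. Does the row handle common causes of dose and outcome? It names no covariate other than dose.

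**Illustration, all inputs assumed**

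Let A be arm, U unmeasured severity (SD 1), M dose (within-arm SD 1) and Y outcome (higher is better):

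- M = a·A + b·U + error
- Y = t·A − c·U + d·M + error

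Then:

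- direct effect = t
- total effect = t + a·d
- coefficient of A adjusted for M = t + a·b·c

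| a | b = dose on U | c | d | t | Total | Direct | Adjusted (formula) | Adjusted (simulated, n = 400,000) |
|---|---|---|---|---|---|---|---|---|
| −0.5 | 0.5 | 0.5 | 0 | 0 | 0 | 0 | −0.125 | −0.127 |
| −0.5 | 0.5 | 0.5 | 0.3 | 0.3 | 0.15 | 0.3 | 0.175 | 0.176 |
| −0.8 | 0.7 | 0.7 | 0.3 | 0.3 | 0.06 | 0.3 | −0.092 | −0.092 |
| −0.5 | 0 | 0.5 | 0.3 | 0 | −0.15 | 0 | 0 | 0.004 |
| 0 | 0.5 | 0.5 | 0.3 | 0 | 0 | 0 | 0 | 0.005 |

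- Row 1: no effect of any kind, yet −0.5 × 0.5 × 0.5 = −0.125. The unadjusted simulated estimate is −0.002.
- Row 2: the adjusted value is neither the total nor the direct effect.
- Row 3: the sign is reversed against both.
- Row 4: with no common cause, the adjusted value is the direct effect but not the total effect.
- Row 5: if albumin does not move dose, there is no bias.

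Range for row 1: with b = c from 0.3 to 0.6, the formula gives −0.5 × 0.09 = −0.045 to −0.5 × 0.36 = −0.18. The sign follows the product a·b·c. If albumin raised the dose by 0.5, or if sicker patients received less furosemide (b = −0.5), row 1 would become +0.125.

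On units: when Y is scaled to a within-arm SD of 1 and d = 0, c is the size of the severity-outcome correlation and −0.125 is in SDs. The simulation set the residual SD to 1, so in row 1 the within-arm SD of Y is √1.25 = 1.12 and −0.125 is 0.11 of it.

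Two-sided 5% rejection of the adjusted test under row 1 (3,000 simulated trials each): 7.5% at N = 50, 24% at N = 500 and 41% at N = 1000. Control runs with a = 0 gave 5.9%, 4.7% and 5.8%. The two larger sizes are assumptions. The bias does not shrink with N, so the false-positive rate grows.

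**The case against.** The strongest reply is that the row states its own question. It asks openly about an effect beyond dose, so taking out the part that runs through dose is its purpose. It is one of three sensitivity rows, the main analysis is intention to treat, and no clinical outcome analysis is planned for the pilot. Confounders collected at baseline might be named in a fuller analysis plan.

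Much of this stands, and it limits the point. Several stronger readings are tempting but not supported:

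- *That the trial's main result or the pilot's verdict is biased.* Neither uses this row.
- *That the row will show spurious harm.* That is one direction under assumed inputs. The expected reduction in interruptions could push dose, and so the bias, the other way.
- *That the adjusted coefficient must be wrong.* Its bias for the direct effect is conditional, as rows 4 and 5 of the table show.
- *That the protocol says dose is titrated to severity.* It says only that the caregiving team prescribes it.
- *That the plan intends to regress dose on itself.* The all-outcomes entry does so if read literally, but it is a condensed table cell and merely needs an exclusion.

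What the reply does not meet is that the article states this analysis, its covariate and its conclusion outright. A fuller plan could add confounders. It would not turn a direct-effect model into a sensitivity check of the total effect. Nor is a baseline dose a natural reading: no pre-randomisation dose is defined, and baseline adjustment has its own row.

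**Conclusion.** The point holds in a limited form and should be acted on. Adjusting for treatment-period furosemide dose does not test the robustness of the randomised comparison, and by itself does not support the direct-effect conclusion attached to it. That rests on the article's own text: dose follows randomisation, is clinician-set, is hypothesised to differ by arm and is an outcome.

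That the direct-effect estimate is actually biased rests on two further conditions: that albumin changes dose, which the plan hypothesises, and that some uncontrolled factor drives both dose and outcome, which is likely with clinician-set dosing but is inferred. Size and direction are unknown. The figure of about −0.125 SD is an illustration only. The consequence is confined to the analyses pre-specified for the definitive trial.

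**What to change.** Either remove the row "Adjusted for dose of furosemide" from the sensitivity analyses, or move it to a clearly labelled exploratory mediation analysis that:

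- adjusts for the baseline severity already collected (APACHE-2 and SOFA at randomisation);
- states its assumption of no unmeasured common cause of dose and outcome;
- excludes furosemide dose from the outcomes analysed;
- is not used to confirm or undercut the main result.

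Keep total furosemide dose as an outcome reported by arm. A ratio such as urine output per mg of furosemide is not a safe substitute: its denominator is also set after randomisation and becomes unstable when furosemide is held.

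The cost is one row of Table 2, with no change to data collection. The small downside is that the direct-effect question is then answered only as exploratory. The article reports that recruitment has not begun, so the change can be made before any data exist.
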